### Randomization and allocation concealment

The randomization list will be generated by an epidemiologist using web software (www.random.org), with blocks of random sizes that will not be disclosed to ensure concealment. Groups will be generated by stratified randomization per age (35–50 and 51–65 years) and baseline systolic ambulatory blood pressure in order to provide homogeneity on these prognostic factors. The epidemiologist will not participate in the recruitment or assignment to intervention sessions. The outcome assessors and data statistical analyses will be double masking to the endpoints of study. In contrast, participants and the beach tennis instructors will be blinded to the randomization list until the moment of assignment.

### Strategies of study retention

During study period, we will use phone calls/ text messages to inquire for any adverse events or if a participant misses a beach tennis session reschedule missed sessions. The phone calls schedule will be ceased for participants declaring their withdrawal from the study. Thereafter, we will make available to participants three non-consecutive days in different time and turn to perform the interventions.

Measures of adherence to beach tennis intervention will be reported as group averages and operationalized as attendance and compliance. Attendance will be monitored through session’s frequency recording and will be treated as the percent of beach tennis intervention sessions experienced by a participant given the total number of scheduled sessions. Adherence will be treated as the percent of intervention sessions fully accomplished without protocol deviations given the total number of scheduled sessions.

### Safety assessments

Data on all adverse events will be collected and included in medical reports, which will be forwarded to the health authorities. To ensure patient safety, we will monitor any adverse events occurred during the study, and all participants will be monitored throughout the study follow up and during 4 weeks after study finished.

### Statistical analysis

The endpoints will be analyzed using a full analysis set including all randomized participants, therefore allowing intention-to-treat analyses. A second set of per-protocol analysis will be performed including participants that completed the trial with adherence to at least 80% of the beach tennis intervention sessions (≥ 19 sessions for participants allocated in the BTT program).

Data distribution will be analyzed using Shapiro-wilk test with analysis of histogram and Q-Q plots in combination. Data will be expressed as means and standard error for variables with normal distribution or medians and interquartile range for non-normal distributions and 95% confidence intervals (95%CI). Ambulatory blood pressure will be analyzed as daytime, nighttime and 24 h systolic and diastolic blood pressure. Primary and secondary outcomes will be analyzed using generalized estimating equation model (GEE) for correlated measures. Adjustment for multiple comparisons will be accomplished using Sequential Bonferroni test. All analysis will be conducted using SPSS Statistics for Windows, version 18.0 (IBM corp., Armonk, NY, USA).

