### Outcome measurements

Outcomes will be assessed for all randomized participants before and after the intervention sessions, irrespective of attendance or completion status. For participants who drop-out of the study at any time after the randomization, researchers will use contact information to invite such participants to undergo the end-study outcome assessments (12 weeks after the beginning of intervention).

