### Sample size and power calculation

Sample size for the primary outcome was calculated using estimates of effect sizes from randomized clinical trial with similar design [14]. This estimation was set a priori based on a behavioral intervention for middle-aged patients with hypertension and analyzed in an intention-to-treat approach. A sample size of 42 individuals with hypertension on 2:1 ratio (BTT, *n*= 28) and (Con, *n*=14) allowing a dropout rate of 10%, will be able to detect a difference of 4 ± 6 mmHg in systolic 24 h blood pressure between groups. Statistical power was set at 90% including a type I error rate of 5%. WinPepi software calculator was used to estimate the sample size [35].

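### Counting everyone in the analysis set does not protect an unweighted GEE from missing 12-week recordings: it can be biased if the working correlation is independence and loss differs by arm

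*Protocol article*

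**What the plan says.** The Statistical analysis section defines the main analysis set and draws a conclusion from it: "The endpoints will be analyzed using a full analysis set including all randomized participants, therefore allowing intention-to-treat analyses". The method follows: "Primary and secondary outcomes will be analyzed using generalized estimating equation model (GEE) for correlated measures". It names no working correlation, weighting or imputation. The only other analysis is per-protocol, at 80% adherence.

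On collecting the outcome, the Outcome measurements section sets a sound aim: "Outcomes will be assessed for all randomized participants before and after the intervention sessions, irrespective of attendance or completion status". For people who leave, "researchers will use contact information to invite such participants to undergo the end-study outcome assessments". The section on study retention adds a limit: "The phone calls schedule will be ceased for participants declaring their withdrawal from the study". The sample size section describes "A sample size of 42 individuals with hypertension on 2:1 ratio" (28 beach tennis, 14 control), "allowing a dropout rate of 10" per cent, and says that this number "will be able to detect a difference of 4 ± 6 mmHg".

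**The concern.** Analysing everyone as randomised and having a 12-week value for everyone are different things. A participant with a baseline recording and no 12-week recording belongs to the full analysis set, but contributes to the training effect only through what the model does with the baseline value. The article's step from analysis set to intention-to-treat passes over this.

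The model it names matters here. Unweighted GEE is in general valid only under missing completely at random. With two recordings per person and an independence working correlation, each arm's estimated change is the 12-week mean of those who returned minus the baseline mean of all who were randomised. If those lost had unusual baseline pressures, the arm mean moves although nobody's pressure has changed. One arm attends sport sessions twice a week and the other is told to change nothing, so reasons for leaving may well differ by arm. The primary outcome is at stake, in a trial with a 4 mmHg target. The per-protocol analysis selects further on completion and would not reveal the problem.

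**Working it through.** **Inputs from the protocol article.** 28 beach tennis and 14 control; 10% dropout allowance (10% × 42 = 4.2 people); target difference 4 mmHg; SD 6 mmHg, read here as the SD of change. The article gives no figure for bias or for missing recordings, so there is none to reproduce. The stated 42 does not follow from its own inputs (two-sided: 108, or 120 after 10% dropout). That is a separate matter, and only the 4 and the 6 are used below.

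**Assumptions, not in the documents.** 24 h systolic SD *s* of 8, 10 or 12 mmHg at both times. The correlation *r* is set so that the change SD is 6: 6 = s√(2(1 − r)), so r = 1 − 36/(2s²). This gives 0.719, 0.82 and 0.875. Loss occurs in beach tennis only, with log-odds rising by *b* = 0.5 or 1.0 per SD of baseline pressure and the intercept set so that average loss *p* is exactly 10% or 20%.

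**Step 1: bias under independence.** Let *m* be the mean standardised baseline of those who return. Their expected 12-week mean is shifted by r·s·m, while the baseline mean of everyone is not shifted. So

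bias = r × s × m, with m = −[p/(1 − p)] × (mean standardised baseline of those lost).

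Numerical integration over a normal baseline gives the mean for those lost:

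| p | b | Mean of lost (SD units) | m |
|---|---|---|---|
| 10% | 0.5 | 0.440 | −(0.1/0.9) × 0.440 = −0.049 |
| 10% | 1.0 | 0.817 | −(0.1/0.9) × 0.817 = −0.091 |
| 20% | 0.5 | 0.385 | −(0.2/0.8) × 0.385 = −0.096 |
| 20% | 1.0 | 0.693 | −(0.2/0.8) × 0.693 = −0.173 |

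**Step 2: results (mmHg).**

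| p | b | s = 8 | s = 10 | s = 12 |
|---|---|---|---|---|
| 10% | 0.5 | −0.28 | −0.40 | −0.51 |
| 10% | 1.0 | −0.52 | −0.74 | −0.95 |
| 20% | 0.5 | −0.55 | −0.79 | −1.01 |
| 20% | 1.0 | −1.00 | −1.42 | −1.82 |

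Example: 0.82 × 10 × (−0.0908) = −0.74. Against 4 mmHg, the range is 7% to 24% at 10% loss (0.28/4, 0.95/4) and 14% to 45% at 20% (0.55/4, 1.82/4). A large simulation (40,000 and 20,000 participants, no true effect) at s = 10, b = 1.0 and 20% loss gave −1.41, in agreement. With a steeper slope of 2 per SD it gave −2.16.

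**Step 3: direction.** If low-baseline players leave instead, *b* is negative and every entry changes sign. A real effect would then be partly hidden.

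**Step 4: loss alike in both arms.** *m* is then the same in each arm and cancels. The large simulation with 10% loss in both arms gave −0.02 to −0.03.

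**Step 5: using the within-person correlation.** The 12-week mean then becomes the returners' mean plus r × (baseline mean of all − baseline mean of returners). In the example this adds back 0.82 × 0.908 = 0.74, which cancels the bias. Simulated trials of 28 v 14 with an exchangeable GEE (s = 10, r = 0.82, 15–20% loss in beach tennis only) gave −0.05 to +0.15, with simulation error of about 0.15 to 0.2.

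**Step 6: scale.** The standard error of the difference, before any loss, is 6 × √(1/28 + 1/14) = 1.96 mmHg. The largest table entries are 0.95/1.96 = 0.48 of a standard error at 10% loss and 1.82/1.96 = 0.93 at 20%.

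**The case against.** The case on the other side is substantial.

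- **The article does not fix the working correlation and nowhere states a missing-completely-at-random assumption.** Such detail is often left to a fuller protocol or analysis plan. This stands: its absence is not the point. What remains is what is printed, namely the inference from analysis set to intention-to-treat and the choice of GEE. A reader might infer that the plan treats withdrawals as missing completely at random and is therefore biased. The documents do not support that, because a GEE that uses the within-person correlation is close to unbiased for loss that depends on baseline pressure alone.
- **The plan is to measure everyone.** This also stands. Stopping the sessions does not by itself cause a missing value, and the 10% is an allowance in the sample size, not a forecast of missing recordings. The 20% rows double it. Still, an invitation is not a recording, and regular calls stop once someone declares withdrawal.
- **The direction is assumed.** A reader might infer that the bias favours beach tennis. No passage says that high-baseline players will leave, or that losses will differ by arm in that way. Steps 3 and 4 show that the sign can reverse or the bias vanish.
- **The outcome is defined as change from baseline.** If individual changes were analysed, drop-outs would contribute nothing, and the mismatch between two groups of people could not arise. At s = 10, b = 1.0 and 10% loss, the bias would be (1 − 0.82) × 0.908 = +0.16 mmHg, against training. The reference to correlated measures points more naturally to repeated levels, but the article does not settle it.
- **The bias is below one standard error in every tabulated case.** True, but a larger sampling error does not remove a systematic one.

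**Conclusion.** The point holds in conditional form. Including all randomised participants does not of itself secure an intention-to-treat estimate, and the named method is in general valid only under a stronger missing-data assumption than the trial needs to make. Some missing 12-week recordings are likely, though only among people who decline the final visit.

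Bias in the primary comparison requires two things together: an independence working correlation, and loss that depends on baseline pressure differently in the two arms. Under the stated assumptions it is about 0.3 to 0.95 mmHg at 10% loss and 0.55 to 1.8 mmHg at 20%, in either direction: modest at the low end, material at the high end. It is near zero if either condition fails. The SDs, the loss pattern and the reading of 6 mmHg as the SD of change are assumptions. A claim that the trial will overstate the benefit of training would go beyond the documents.

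**What to change.** Analyse the continuous outcomes with a likelihood-based (REML) repeated-measures model over baseline and 12 weeks, with arm, time and their interaction and an unstructured covariance. It uses the baseline data of those without a 12-week recording, is valid under missing at random, and can be run in the named software.

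If GEE is kept, specify an exchangeable or unstructured working correlation (with two occasions these are the same), or combine it with multiple imputation by arm. In either case, state the missing-data assumption and stop presenting intention-to-treat as a consequence of the analysis set alone.

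The cost is a change of analysis wording, with no new data. A sensitivity analysis for loss not at random, for example giving beach tennis participants without a 12-week recording the control-arm mean change, is optional and takes one extra run.

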#### Primary outcome

The primary outcome is the change from baseline in 24 h, daytime and nighttime systolic and diastolic blood pressure measured by ambulatory blood pressure monitoring at 12 weeks.

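### Randomisation is stratified by age and baseline ambulatory systolic pressure, but the analysis as described names no adjustment for either and reads most naturally as a less precise change-score contrast

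*Protocol article*

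**What the plan says.** - **Allocation** (Randomization and allocation concealment): "Groups will be generated by stratified randomization per age (35–50 and 51–65 years) and baseline systolic ambulatory blood pressure". The stated purpose is to make the arms alike on factors that the article itself calls prognostic.
- **Outcome** (Primary outcome): "The primary outcome is the change from baseline in 24 h, daytime and nighttime systolic and diastolic blood pressure", by ambulatory monitoring at 12 weeks. The Background section expresses the effect as the difference between arms in mean change. The data collection section places the assessments at baseline and at study completion.
- **Model** (Statistical analysis): "Primary and secondary outcomes will be analyzed using generalized estimating equation model (GEE) for correlated measures". No model terms are listed, so covariates are neither included nor excluded. The same section commits to a full analysis set of all randomised participants.
- **Size** (Sample size and power calculation): the plan is for 42 participants, 28 to beach tennis and 14 to control, with 10% dropout allowed for. Of this number the article says that it "will be able to detect a difference of 4 ± 6 mmHg in systolic 24 h blood pressure between groups". The power quoted is 90% and the type I error 5%. The text does not say whether the 6 mmHg is the SD of a change or of a single measurement.

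**The concern.** The design uses two prognostic factors to allocate participants, and the analysis text does not carry them forward. With a baseline and a 12-week value per participant, a GEE for correlated measures is most naturally a model in which both values are responses and the treatment effect is the group-by-time term. If baseline means are left free in each arm and the data are complete, that term is exactly the difference between arms in mean change. Baseline is then used as a response and not as a covariate.

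Two things are lost. The change-score contrast has a larger variance than a baseline-adjusted one whenever the correlation between the two time points is below 1. And when randomisation is stratified on a prognostic factor that the model leaves out, the model's standard errors do not credit the balance achieved, so intervals are wider than the design warrants. With 14 controls, a half-width of about 4 mmHg is as large as the 4 mmHg difference the trial is meant to detect, so avoidable width matters.

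**Working it through.** **1. The plan's own sample size.** Inputs from the sample size section: difference 4, SD 6, ratio 2:1, power 90%, type I error 5%, taken as two-sided. By the normal approximation the control arm needs

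n = (1 + 1/2)(1.960 + 1.282)² × 6² / 4² = 1.5 × 10.51 × 2.25 ≈ 35.5, so 36.

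That gives 36 + 72 = 108 evaluable participants, or 120 with 10% dropout, against the stated 42. The stated figure is not reproduced. This is a separate problem; it matters here because it shows how little precision there is to spare.

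**2. Change score against baseline adjustment.** Let σ be the SD at each time point (assumed equal) and ρ the correlation between baseline and 12 weeks. The documents give no ρ; 0.5 to 0.8 is assumed. Per participant:

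- change score: 2σ²(1 − ρ)
- adjusted for baseline: σ²(1 − ρ²)
- ratio, adjusted to change: (1 + ρ)/2

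**3. Into the trial's numbers.** Read 6 mmHg as the SD of change. The adjusted SD is 6√((1 + ρ)/2). Two-sided 5% t test, with two degrees of freedom spent on covariates in the adjusted rows. The 25/13 column is 28 and 14 less 10%, rounded.

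| Analysis | Variance ratio | SD (mmHg) | 95% CI half-width, 28/14 (mmHg) | Power, 28/14 | Power, 25/13 |
|---|---|---|---|---|---|
| Change score | 1 | 6.00 | 3.97 | 51.1% | 47.5% |
| Adjusted, ρ = 0.5 | 0.75 | 5.20 | 3.44 | 63.0% | 59.0% |
| Adjusted, ρ = 0.6 | 0.80 | 5.37 | 3.56 | 60.2% | 56.3% |
| Adjusted, ρ = 0.7 | 0.85 | 5.53 | 3.67 | 57.7% | 53.8% |
| Adjusted, ρ = 0.8 | 0.90 | 5.69 | 3.77 | 55.3% | 51.5% |

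Example for the first row: SE = 6√(1/28 + 1/14) = 1.964; half-width = 2.021 × 1.964 = 3.97. These t-based figures approximate what the GEE would report.

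**4. What stratification has already removed.** The change-score and adjusted estimates differ by (1 − ρ) times the baseline difference between arms. Stratifying on baseline systolic pressure shrinks that difference. The article gives no cut-point, so take an ideal case: a perfectly balanced median split of a normal baseline, which leaves 1 − 2/π ≈ 36% of the baseline variance within strata. The true variance ratio becomes

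(1 − ρ²) / [(1 − ρ²) + 0.36(1 − ρ)²] = 0.89, 0.92, 0.94, 0.96 at ρ = 0.5, 0.6, 0.7, 0.8.

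So in that ideal case the real saving for systolic pressure is 4 to 11%. The rest of the 10 to 25% in step 3 is over-wide reported standard errors. Incomplete blocks would move the true ratio back towards step 3.

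**5. Sensitivity to the meaning of 6 mmHg.** If it is the SD of a single measurement, the SD of change is 6√(2(1 − ρ)). With 28/14 (normal approximation), power is:

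| ρ | Change score | Adjusted |
|---|---|---|
| 0.3 | 41% | 57% |
| 0.5 | 53% | 65% |
| 0.7 | 75% | 81% |
| 0.8 | 90% | 92% |

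The direction is the same, but the level and the size of the gain depend on which SD is meant.

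**The case against.** The strongest objection is that the statistical section names a class of model and no terms. The article condenses a fuller protocol, and a covariate list is commonly left to that protocol or to the analysis plan. A reader might infer that the GEE uses neither stratification factor. The text does not support that as fact: it is silent on covariates, and baseline pressure most plausibly enters the model as one of the two correlated responses. If baseline means are constrained equal across arms, or baseline is already a covariate, little or nothing is lost. This part of the objection stands and limits the point to the analysis as described.

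A reader might also infer that the unadjusted contrast is biased, or that chance imbalance in systolic pressure is left uncontrolled. Neither follows. A change-score contrast is valid under randomisation, and stratification already limits imbalance in ambulatory systolic pressure. Outcomes not closely related to the stratification factors have less of that protection.

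Finally, a model of the 12-week value alone drops anyone without follow-up unless a missing-data rule is given, which sits badly with the full analysis set and the 10% dropout allowance. That is a fair constraint on the remedy, and the fix below respects it.

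What survives is more than a gap in detail. The estimand, the two assessments and the repeated-measures model together point to a change-score contrast, and a more precise one is available from data already collected.

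**Conclusion.** The concern holds for the analysis as described. On its natural reading the plan gives a valid but less efficient contrast, with standard errors that do not credit the stratified design. This is a question of efficiency and of consistency between design and analysis, and a change worth making rather than an essential one.

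For 24 h systolic pressure with 28 and 14 participants, adjustment shortens the reported half-width by about 0.2 to 0.5 mmHg and adds about 4 to 12 points of power. These sizes rest on three assumptions: 6 mmHg is the SD of change, ρ lies between 0.5 and 0.8, and the GEE is an unconstrained group-by-time model. The true reduction in variance for systolic pressure is smaller than the reported one, by an amount that depends on how well the strata balance.

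A reader might infer that adjustment rescues the sample size. On the SD-of-change reading it does not: power stays well below the stated 90%.

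**What to change.** Add one sentence to the Statistical analysis section: for each outcome, the arm effect at 12 weeks will be estimated with its 95% CI, adjusted for that outcome's own continuous baseline value and for age stratum, and for outcomes other than ambulatory systolic pressure also for baseline ambulatory systolic pressure.

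Either of two forms will do:

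- covariates in a model of the 12-week value, with a stated way of keeping randomised participants who lack that value; or
- the planned GEE with baseline means constrained equal across arms and a working correlation other than independence, so that the baseline response contributes to the arm effect.

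Both must keep all randomised participants, in line with the full analysis set. Stating whether the 6 mmHg is the SD of change would let the gain be sized properly.

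The cost is two or three degrees of freedom; every covariate is already collected. If the full protocol or analysis plan already specifies this, no change is needed.

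### GEE with 28 and 14 participants, no stated small-sample correction and no baseline adjustment does not hold the nominal error rates: about 7% for outcomes unrelated to the strata, roughly 4.4–6.6% for 24 h systolic BP

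*Protocol article*

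**What the plan says.** Under Statistical analysis, the protocol article fixes one method for everything: "Primary and secondary outcomes will be analyzed using generalized estimating equation model (GEE) for correlated measures". It adds that "The endpoints will be analyzed using a full analysis set including all randomized participants", applies Sequential Bonferroni to multiple comparisons, and names the software: "All analysis will be conducted using SPSS Statistics for Windows, version 18.0". It does not state the type of standard error, any small-sample correction, the reference distribution or any covariates.

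Under Sample size and power calculation, the size is "A sample size of 42 individuals with hypertension on 2:1 ratio", that is 28 and 14, "allowing a dropout rate of 10"%. The error rate is nominal: "Statistical power was set at 90% including a type I error rate of 5"%.

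Under Primary outcome: "The primary outcome is the change from baseline in 24 h, daytime and nighttime systolic and diastolic blood pressure". That is six measures, each taken at baseline and at 12 weeks.

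Under Randomization and allocation concealment, allocation is stratified by two age bands and by baseline systolic ambulatory BP. The BP cut-point is not given, and the block sizes are deliberately undisclosed.

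**The concern.** GEE inference usually rests on the sandwich variance and a normal or chi-square reference. Both are justified when there are many independent clusters. Here each participant is a cluster, so the control arm supplies 14, or 12 to 13 after the allowed dropout. At that size the uncorrected sandwich variance is biased low, and a normal reference ignores the uncertainty in the variance estimate.

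A second feature acts in the other direction. Stratifying on a variable that predicts the outcome makes the arms more alike than simple randomization would. An analysis that ignores that variable does not credit this balance, so its standard error comes out too large. For systolic BP the two errors partly cancel, by an amount the plan does not control.

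At stake is whether the reported p-values and 95% intervals mean what they say. Sequential Bonferroni lowers the threshold but does not repair the standard error or the reference distribution.

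**Working it through.** **Figures in the plan.** The article gives no operating characteristics for the GEE beyond the nominal 5% and 95%. The figure of 42 does not enter the check except as arm sizes. It does not reproduce from the stated inputs ("will be able to detect a difference of 4 ± 6 mmHg in systolic 24 h blood pressure between groups"). Reading 6 as the SD, the control arm needs 1.5 × (1.960 + 1.282)² × 36/16 ≈ 35.5, so 36 + 72 = 108, or 120 with 10% dropout. That is a separate matter; with equal SDs in the two arms, the error rates below do not depend on the SD.

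**Inputs.** Arm sizes 28/14 from the article. About 25/13 or 25/12 after 10% dropout. Two visits. Assumed: normal data, a group-by-visit model without covariates, uncorrected sandwich SE, Wald test at 1.96.

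**Step 1, bias of the sandwich variance by hand.** With complete data the GEE contrast is the difference in mean change. Its sandwich variance is Σ(d − d̄)²/n² per arm, with expectation (n − 1)/n times the true value. At 28/14:

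(27/784 + 13/196) / (1/28 + 1/14) = 0.1008/0.1071 = 0.94; square root 0.97.

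The mean of the estimated SE itself is slightly lower, at 0.96 of the true SE in simulation.

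**Step 2, error rate without stratification** (400,000 simulated trials per row, SD of change 6 in both arms):

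| Arms | Type I error | Coverage | Mean SE / true SE |
|---|---|---|---|
| 28/14 | 6.8% | 93.2% | 0.96 |
| 25/13 | 7.0% | 93.0% | 0.96 |
| 25/12 | 7.2% | 92.8% | 0.95 |

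Fitted exchangeable GEEs (4,000 fits each, correlation 0.5) gave 6.4% with complete data and 7.1% with 10% of week-12 values missing at random. Monte Carlo error is about 0.4 points.

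**Step 3, splitting the cause at 28/14.** Uncorrected sandwich with z: 6.8%. Unbiased variance with z: 6.0%. Unbiased variance with Satterthwaite t: 5.0%. Of the 1.8-point excess, 0.8 comes from the variance and 1.0 from using z.

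**Step 4, adding the stratification for systolic BP.** Let ρ be the within-person correlation, with equal variances at the two visits. The covariance of change with baseline is (ρ − 1)σ² and the variance of change is 2(1 − ρ)σ², so baseline explains (1 − ρ)²/[2(1 − ρ)] = (1 − ρ)/2 of the variance of change. A median split carries 2/π ≈ 0.637 of a normal baseline. With perfect balance on the split, the true variance of the contrast is multiplied by 1 − 0.637(1 − ρ)/2, and the 0.96 from Step 1 is divided by its square root:

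- ρ = 0.3: 1 − 0.637 × 0.35 = 0.777; 0.96/0.881 ≈ 1.09
- ρ = 0.5: 1 − 0.637 × 0.25 = 0.841; 0.96/0.917 ≈ 1.05
- ρ = 0.8: 1 − 0.637 × 0.10 = 0.936; 0.96/0.968 ≈ 0.99

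Balance is not perfect with small strata. Simulation with a median split, two age strata and blocks of 3 or 6 (all assumed), with and without dropout, gave SE ratios of 0.98 to 1.08 and type I error of 4.4% to 6.6%, rising with ρ.

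**Step 5, the strictest Bonferroni level.** If the six primary measures form one family (assumed), the first step tests at 5%/6 = 0.83%. The actual error is 1.6–1.7% without the stratification effect, and 0.8–1.5% for systolic BP with it.

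**Step 6, the alternative.** A baseline-adjusted linear model with a t reference ran at 4.7–5.2% in the same kind of simulation.

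**The case against.** The strongest reply is that the article fixes only the model class. A journal article commonly leaves the covariance estimator and degrees of freedom to the full protocol or analysis plan, and one naming a bias-corrected SE with a t reference would settle most of the point without contradicting the article. That stands, so the size given here is conditional on uncorrected robust Wald inference. The other uncorrected choice, a model-based SE with z, ran at 5.7% in closed form and 6.2–6.8% in fitted GEEs with equal variances, so it does not hold 5% either. The point survives because the pairing of GEE with 14 controls is stated and a better method for it is available.

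Three stronger readings are tempting and not supported:

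- *A reader might infer that every test in the trial, including 24 h systolic BP, runs at about 7%.* The stratified randomization contradicts this for systolic BP, where the error may fall on either side of 5%.
- *A reader might infer that the standard error is simply too small.* That is about half of the excess where there is one. For systolic BP the SE may be too large.
- *A reader might infer that dropout biases the GEE.* Unweighted GEE does generally rely on data missing completely at random. But under Outcome measurements the article plans week-12 assessment of all randomized participants, including those who drop out, and nothing in the documents gives a size for any remaining bias. This is secondary.

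It is also fair to say that GEE for two correlated measures is a legitimate method and that the departure is at most about two percentage points at the 5% level.

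**Conclusion.** The point holds in a limited form. With 28 and 14 participants, uncorrected robust GEE inference without baseline adjustment gives a type I error of about 7% and coverage of about 93% for outcomes little related to age and baseline systolic BP. For 24 h systolic BP it gives roughly 4.4–6.6%. Outcomes between these two cases should fall between the two results.

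This rests on the standard estimator being used, which the article does not say, and on normal data. The systolic range also rests on correlations of 0.3 to 0.8, a median split and blocks of 3 or 6, none of which the article gives. Unequal spread does not remove the problem: without stratification, the robust test ran at 7.2% with SDs of change of 8 in controls and 6 in the intervention arm, and at 6.5% with the reverse.

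The size is modest and does not invalidate the trial. It is worth correcting because the correction is specific and cheap.

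**What to change.** Analyse each week-12 value with a linear model containing group, the outcome's own baseline value and the stratification factors (age band and baseline systolic ambulatory BP), with t-based inference. Adjusted for baseline, the group effect on the week-12 value is the same as on the change, so the stated primary outcome is kept. Alternatively, use a REML mixed model with Kenward-Roger or Satterthwaite degrees of freedom, which uses all available data under missing at random. If GEE is kept, adjust for baseline and strata, and name a bias-corrected sandwich variance with a t reference. Correcting the variance alone, without the adjustment, would leave the systolic BP analysis conservative when ρ is low.

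One caution applies to the linear model. With 2:1 allocation a pooled variance is sensitive to unequal spread: in the unadjusted comparison a pooled t test ran at 7.4% when controls had SD 8 against 6, and at 3.2% in reverse, while the unequal-variance t test stayed at 5.0–5.1%. Allowing arm-specific residual variances, at least as a sensitivity analysis, deals with this.

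The cost is a change of procedure, new wording, and intervals slightly wider for some outcomes. Conduct, visits and sample size are unaffected.
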